### Data management {19}

#### Data collected on the EDC system

Study outcome measures are entered directly into the REDCap EDC system [39, 40] by participants (online, using a unique access code) or research staff with role-based and password-protected access, who have undertaken the necessary EDC training. The database has passed validation and User Acceptability Testing. Range checks for data values are built into the system. Coded outcomes of observational measures (i.e. sensitivity scales, attachment style and facilitator fidelity to the manual) are only entered into the system by research staff. COS-P report forms are completed by PMHS staff involved in delivery, and entered onto the REDCap system by research staff. PMHS staff have no access to the REDCap system. Monitoring and Source Data Verification will be performed electronically by the Trial Manager or designee as defined in the study monitoring plan. This applies to the COS-P report forms filled out by PMHS staff as well as coding outcomes recorded separately (i.e. sensitivity scales, attachment style and facilitator fidelity to the manual). Once the data are declared clean, i.e. no outstanding queries or issues, and locked by the Study Manager at the end of the study, the CI must complete the signature panel associated with each subject. The Study Manager will request CI approval and then proceed with Database Lock (DBL) and final Data Extract request.

#### Data outside the EDC system

Video recordings of participants and their children (needed to code the sensitivity scales and attachment style) are recorded and stored by research staff outside of the EDC system. Video recordings of intervention sessions are recorded by clinical staff in PMHS and then shared with, and stored by, the research staff at the sponsor. Video recordings of intervention sessions are deleted within 1 year, or when coded if earlier than 1 year. All other video materials and outcome measures are securely archived for 10 years.

#### Qualitative data

Survey data, recordings and transcripts of interviews and focus groups are stored securely online in the UK. Any segments of recording that are unclear will be time stamped by the transcribers, and the research team will check the original recording for accuracy. Recordings will be destroyed upon the study’s completion. Anonymised transcripts and analysis files will be stored securely for 10 years after the study’s completion.

### Confidentiality {27}

Prior to consent, the participant’s name and contact details are shared with the research team by their PMHS once verbal consent to do so has been received. All further personal information is self-reported by participants once included in the trial. All identifiable information will be stored on an encrypted server at the Anna Freud Centre, separate from all outcome data collected. Each participant will be allocated a unique trial ID, and all questionnaire data will be stored in the database according to this trial ID. No identifiable information will be stored in the trial database. Qualitative data will be linked to the main dataset via this unique trial ID number.

Parent participants are informed that all assurances on confidentiality will be strictly adhered to, unless a safeguarding issue regarding potential harm or danger to themselves or another individual becomes apparent. In this case, the concern would need to be referred to the Trial Manager and the relevant healthcare professional. If any risk to the child’s development is identified during the study, the Trial Manager will inform the parent participant and the relevant healthcare professional for further discussion.

### Plans for collection, laboratory evaluation and storage of biological specimens for genetic or molecular analysis in this trial/future use {33}

Not applicable as no biological samples are to be collected.

## Statistical methods

### Statistical methods for primary and secondary outcomes {20a}

The primary analysis aims to estimate the treatment policy estimand. We will use the intention-to-treat principle including all participants who undergo randomisation and have at least one post-randomisation measure at the 3-month, 7-month or 12-month follow-up trial assessment. As a result of this, the number of participants missing from the primary analysis model is expected to be low. A safety population consisting of all participants who attend at least one session of the assigned intervention will be used for the analysis of adverse events. For participants in the TAU arm of the trial, this will be defined as any participant randomised to TAU as per the intention-to-treat population. Baseline characteristics will be summarised by treatment arm and by using suitable measures of central tendencies. The flow of participants through the trial and trial results will be reported according to Consolidated Standards of Reporting Trials (CONSORT).

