#### Birthing parents—qualitative data collection

For the purpose of the qualitative component of the trial, birthing parents assigned to COS-P will be categorised as follows to ensure the relevance of questions asked: *non-starters* (who do not begin the group), *non-completers* (who begin the group but do not receive what is considered a clinical dose, indicated by attending fewer than six sessions) and *completers* (who begin the group and attend at least six sessions). Approximately 3 months after the baseline assessment has been completed, all birthing parents in the intervention arm will be asked to share their views and experiences regarding COS-P, including barriers and facilitators to taking part. Non-starters will be asked to complete a three-item ‘non-starters’ survey to report the reasons. Completers and non-completers will be asked to complete a short experience survey and indicate their interest in taking part in an interview. All surveys can be self-completed or completed with the assistance of a member of the study team, either remotely (by telephone or Teams) or in person. A subsample of completers and all non-completers will be invited by a member of the study team to be interviewed and provided with a PIS and opportunity to ask any questions. Where necessary, the PIS will be translated into alternative languages and interpreter support will be provided to ensure informed consent. Informed consent for the interview will be recorded using Microsoft Forms. A copy of the completed ICF and PIS will be shared with the participant for their records.

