## Data collection and management

### Plans for assessment and collection of outcomes {18a}

#### Data collection and management—quantitative data collection

Participants are offered the possibility of face-to-face (e.g. at home) and virtual trial assessments (via Microsoft Teams) at baseline, 3-month and 7-month follow-up assessments. Baseline trial assessments take place prior to randomisation and the first COS-P session. The trial aims to have no more than 4 weeks between randomisation and the first COS-P group session. As the 12-month follow-up assessment includes the Strange Situation Procedure (SSP; [37]) used for assessing attachment security of the child, this trial assessment takes place in person at a venue local to the participant. Please see Table 2 for further details regarding the data collection schedule. Apart from the video-recorded parent–child interaction and the SSP, participants are given the choice to self-complete the measures online, or to complete them together with a member of the research team. Details on all study measures are provided in Additional File 4.

**Table 2 Tab2:** COSI study data collection schedule

	**Screening**	**Baseline**	**COS-P group (intervention arm only)**	**3-month f/u**	**7-month f/u**	**12-month f/u**
Informed consent	X	X				
CORE-10	X					
Inclusion and exclusion criteria		X				
Demographics		X				
Randomisation		X				
CORE-OM		X		X	X	X
PBQ	X	X		X	X	X
CTQ-SF		X				
DERS		X		X	X	X
ASQ-SE		X		X	X	X
ASQ-3		X		X	X	X
Sensitivity scales		X		X	X	X
CSRI		X		X	X	X
EQ-5D-5L		X		X	X	X
CORE-6D		X		X	X	X
SSP						X
Adverse events		X		X	X	X
Short experience survey			X			
Qualitative interviews			X			

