##### Adverse events

Kaplan–Meier plots are used to examine rates of withdrawals by arm due to any AE. The number of participants requiring social care involvement for the family will be tabulated by arm and Kaplan–Meier plots will be used to examine the time to social care involvement by arm. All AEs are tabulated by arm and severity for the number of participants with at least one adverse event and the number of adverse events. We also calculate odds ratios and incident rate ratios and their 95% CIs for binary and count AE outcomes at SOC level using logistic regression and Zero-Inflated Poisson model or negative Binomial model, following the same framework as the primary analysis model using appropriate generalised linear models with adjustments. The results from these models are then presented graphically along with the raw counts using visual approaches such as the dot plot [42].

A detailed statistical analysis plan will be written prior to data lock and will detail all analysis models and model checks to be performed.

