### Adverse event reporting and harms {22}

At each follow-up data collection time point, participants are invited to complete a short survey regarding solicited adverse events (both physical and social) experienced during the trial. Adverse events which are not considered to be related to the trial intervention or procedures and are not one of the solicited adverse events detailed in this questionnaire will not be recorded in this way. However, unsolicited adverse events may be reported directly by participants during data collection visits or by the participant’s PMHS. All related adverse and serious events will be reported to the Chief Investigators, TSC and DMEC. In the event of a serious adverse event (SAE) occurring during the subject’s participation in the study, the SAE must be reported to the CI and the Sponsor.

All related and unexpected SAEs will be notified to the Research Ethics Committee (REC) and the Sponsor within 15 days of the Chief Investigator becoming aware of the event. Follow-up of participants who have experienced a related or unexpected SAE will continue until recovery is complete or the condition has stabilised.

Annual safety reporting will be included in the Annual Progress reports submitted to the Sponsor and the Research Ethics Committee, on the anniversary of Ethics approval each year. The Annual Progress Report will detail all SAEs recorded.

If any urgent safety measures are taken, the Chief Investigator/Sponsor shall immediately, and in any event no later than 3 days from the date the measures are taken, give written notice to the relevant REC of the measures taken and the circumstances giving rise to those measures.

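### The safety population requires attendance in the COS-P arm only, so the planned between-arm adverse-event comparisons are not protected by randomisation, and the size and direction of the bias are unknown

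*Protocol article*

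**What the plan says.** All references are to the protocol article. Statistical methods for primary and secondary outcomes {20a} sets two entry rules for the adverse-event analyses.

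- **General rule, which governs COS-P:** "A safety population consisting of all participants who attend at least one session of the assigned intervention will be used" for adverse events.
- **TAU:** "For participants in the TAU arm of the trial, this will be defined as any participant randomised to TAU as per the intention-to-treat population". The same section describes the intention-to-treat analysis as "including all participants who undergo randomisation and have at least one post-randomisation measure at the 3-month, 7-month or 12-month follow-up trial assessment".

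The Adverse events section uses this set for comparison as well as description: "We also calculate odds ratios and incident rate ratios and their 95% CIs for binary and count AE outcomes at SOC level". It also plans Kaplan-Meier plots by arm for withdrawals due to adverse events and for time to social care involvement.

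Non-starters are expected. The section on qualitative data collection from birthing parents makes them a separate category, those "who do not begin the group", and gives them their own survey. The first session may come some time after allocation: "The trial aims to have no more than 4 weeks between randomisation and the first COS-P group session".

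**The concern.** Attending a first session is an event after randomisation. Using it as an entry condition in one arm, with nothing equivalent in the other, means that the two sets are no longer the groups that randomisation formed. Suppose social care becomes involved between allocation and the first session and the parent never attends. In COS-P that event leaves the analysis. In TAU it is counted, provided the parent completes a follow-up measure. More generally, if parents who do not start have a different event risk from those who do, the odds ratio will differ from 1 even when COS-P has no effect on harms.

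This is the only comparative harm analysis that the article states, and the section on additional analyses {20b} announces no others. The primary efficacy analysis targets a treatment policy estimand, so benefit and harm would also be compared in differently defined populations.

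**Working it through.** **What the article gives.** It states no non-starter rate, adverse-event risk or expected harm ratio, so there is no figure of its own to reproduce here. It does give the recruitment target of 246 COS-P and 123 TAU participants (Sample size {14}). Everything else below is an assumption, shown as a range.

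**Assumptions.** No true effect of COS-P on adverse events. Overall event risk p = 0.30 in both arms as randomised. Non-starter share q = 0.10 to 0.20. Ratio of non-starter to starter risk r = 0.5 to 2.

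**Size of the sets.** The COS-P set falls from 246 to 246 × 0.90 ≈ 221 at q = 0.10, and to 246 × 0.80 ≈ 197 at q = 0.20. No TAU participant is removed for non-attendance.

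**Formulas.** The overall risk is a mixture, p = (1 − q)·s + q·r·s, where s is the risk among starters. Hence s = p / (1 − q + q·r). The planned comparison sets s against p, so OR = [s/(1 − s)] / [p/(1 − p)], with p/(1 − p) = 0.30/0.70 = 0.4286.

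| q | r | Starters' risk s | Risk difference (points) | Odds ratio |
|---|---|---|---|---|
| 0.10 | 0.5 | 0.30/0.95 = 0.316 | +1.6 | 1.08 |
| 0.10 | 1 | 0.30/1.00 = 0.300 | 0.0 | 1.00 |
| 0.10 | 2 | 0.30/1.10 = 0.273 | −2.7 | 0.88 |
| 0.20 | 0.5 | 0.30/0.90 = 0.333 | +3.3 | 1.17 |
| 0.20 | 1 | 0.30/1.00 = 0.300 | 0.0 | 1.00 |
| 0.20 | 2 | 0.30/1.20 = 0.250 | −5.0 | 0.78 |

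Compared by randomised arm, the true odds ratio in every row is 1.00.

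**When there is a true harm.** Let attendance add 10 points to the starters' risk, with q = 0.20 and equal underlying risk (r = 1). The planned set gives 0.40 − 0.30 = +10 points. By randomised arm, COS-P has 0.80 × 0.40 + 0.20 × 0.30 = 0.38, which is +8 points. With r = 2, starters have 0.25 + 0.10 = 0.35 and the planned set gives +5 points. By randomised arm it is 0.80 × 0.35 + 0.20 × 0.50 = 0.38, again +8. The planned set can therefore show more harm or less harm than the randomised comparison, depending on r.

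**The case against.** An exposure-based safety set is a common convention with a sound reason behind it: unexposed participants dilute a harm caused by exposure. The +10 against +8 example shows this, and it is why the attended set should be kept. It does not justify a between-arm ratio when the comparator has no matching condition.

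The models carry the primary model's adjustments, including baseline CORE-OM, which may remove part of any imbalance in baseline severity. They cannot be relied on to remove selection driven by what happens between allocation and the first session. The distortion may also be modest beside sampling error. At q = 0.15 and r = 2, s = 0.30/1.15 = 0.261 and the odds ratio is 0.82, a shift of about 0.19 on the log scale. The standard error with about 209 against 123 participants is about 0.25. That limits the weight of the point, but a systematic shift is not covered by the confidence interval.

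Two stronger readings are tempting and should not be taken.

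- **That every TAU participant is kept.** TAU entry refers to the intention-to-treat population, which the same section limits to those with a post-randomisation measure. The asymmetry is the attendance condition.
- **That events are captured unequally.** The article says that "unsolicited adverse events may be reported directly by participants during data collection visits" or come through the service, and COS-P adds weekly contacts. But both arms are under service care, the solicited survey is offered at each follow-up with no difference by arm, and the article does not say that unsolicited events enter the models.

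**Conclusion.** The point holds: the entry rule, as written, conditions one arm on post-randomisation attendance, and the adverse-event and social-care comparisons built on it are not randomised comparisons. With no true effect and the assumptions above, the expected odds ratio runs from about 0.78 to about 1.17. The non-starter share, the overall risk and the risk ratio are all assumed, so this range is an illustration and not an estimate.

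A reader might infer that the rule leans in favour of COS-P, on the ground that sicker parents fail to start. The documents do not establish this. They do not say why parents fail to start; a survey is planned to find out. The section on adherence deals largely with practical barriers. The deterioration example in the discontinuation criteria concerns stopping the allocated intervention, and a parent who stops after one session remains in the safety set. If non-starters have lower risk, the bias runs against COS-P.

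Severity is moderate. The primary outcome and its population are untouched, and the reporting of related and serious events to oversight does not depend on the analysis set.

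**What to change.** State in the statistical analysis plan that comparative adverse-event analyses, including the Kaplan-Meier plots and social care involvement, are made by randomised arm with one entry rule for both: all randomised participants with any post-randomisation adverse-event data, COS-P non-starters included. Keep the attended-at-least-one-session set as a supplementary analysis for COS-P, and report the number of non-starters.

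The cost is about two sentences. The article says that the detailed analysis plan will be written before data lock. No new data collection is needed: solicited events are surveyed at each follow-up whether or not sessions were attended, and follow-up continues for those who withdraw from the intervention only.

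There are two limits. Including non-starters can dilute a harm caused by attendance, which the supplementary set would show. Participants who withdraw from all procedures give no further data, so the comparison still depends on who is followed up, but the rule is then the same in both arms.

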#### Primary analyses

For the primary analysis, we will use a mixed effects linear regression model to estimate the mean difference in CORE-OM between arms over 3-, 7- and 12-month follow-up trial assessments and a Bayesian mixed effects linear regression model using vague priors. From the Bayesian model, we will obtain the posterior probability of the intervention being superior to TAU, as well as the posterior probability of treatment effect exceeding the pre-specified Minimal Clinically Important Difference (MCID) of 5 points in the CORE-OM. In the mixed effects linear regression model, participants and recruitment cohort (in the intervention arm to account for group clustering in one arm) will be included as random intercepts. Fixed effects in the model will be intervention arm, site, and baseline CORE-OM, infant sex, infant age and infant first born status [36]. The mean difference in CORE-OM over 3-, 7- and 12-month follow-up trial assessments will be reported, with accompanying 95% confidence intervals, and *p*-value will be presented.

A Bayesian mixed effects linear regression model will be fitted and follows the same form as the frequentist mixed effects linear regression model described above. We will use vague (large variance) normal priors for regression coefficients and inverse-gamma priors for the error variance and for the variance of random intercepts which have been chosen to be uninformative. Model convergence will be investigated for the parameters of primary interest (specifically the treatment effect estimate) using graphical diagnostics. The intervention effect will also be estimated at the 3-, 7- and 12-month follow-up trial assessments using a Bayesian mixed effects linear regression model with a model including time point and adding a time-by-intervention arm interaction.

#### Sensitivity analysis on primary

The analysis using mixed effects linear regression model will be valid under a Missing At Random (MAR) assumption. If the proportion of participants that have no post-randomisation measures is above 5%, we will conduct an additional analysis using controlled multiple imputation to examine the impact of Missing Not At Random (MNAR).

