With 104 parents in the control arm and 208 parents (*N* = 312) in the intervention arm, we will have 90% power to detect a minimally clinically important average mean item change of 0.147, assuming a *SD* of 0.5, three repeated measurements with a correlation of 0.35 and using a 5% significance threshold. Previous small trials have reported 15–20% missing at follow-up [20, 21] by the end of the trial. In the current trial, participants will be rigorously followed up and those who have at least one post-randomisation measurement will be included in the analysis. We therefore assume it is reasonable to obtain one post-randomisation measurement of the primary outcome in at least 90% and therefore factor in 10% missing. As the intervention is delivered in groups, there is potential for clustering of the outcomes in the active arm. We do not have reliable data to inform us what the intra-cluster correlation (ICC) coefficient in this context is. However, even if the ICC were large (> 0.05), the intervention group size is small so the effect will be limited. It is not expected this clustering will greatly affect the results. To protect against any potential effect in the absence of information, we inflated the sample size by an additional 5% to take into account the potential for one-arm clustering. Taking into account the potential for clustering (5%) and missing data (10%), we will aim to recruit a total of 369 birthing parents (*n* = 246 and *n* = 123 per arm). This was calculated using the time-averaged difference test in the PASS statistical software.

For the embedded qualitative component, we have estimated interviewing 20–30 completers, which is consistent with other HTA-funded process evaluations (e.g. ISRCTN12655391, ISRCTN34701576) and aim to interview all non-completers. The total sample size will be guided by principles of data saturation concerning meaning [35] and with emphasis on data quality. It is therefore not possible to determine the exact sample size in advance. Focus groups with staff will use total population sampling, i.e. inviting all members of those groups.

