### Plans to promote participant retention and complete follow-up {18b}

It is intended that newsletters regarding the trial will be shared with participants in the study to promote engagement. Parent participants also receive a £10 voucher per trial assessment as reimbursement for their time. An additional £20 voucher will be provided as reimbursement for parent participants who take part in an interview for the qualitative assessment.

If a participant chooses to withdraw from all study procedures, no further outcome data will be collected. Any information regarding the reason for the withdrawal will be recorded in the trial database. If a participant chooses to withdraw from the study intervention only, all future follow-up visits will be completed as per the study protocol.

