### Methods in analysis to handle protocol non-adherence and any statistical methods to handle missing data {20c}

As we target the treatment policy estimand, we will include all participants in the analysis including those that did not adhere to the protocol. A supplementary analysis will be performed using a counterfactual approach to estimate the treatment effect in those that adhered to the treatment protocol. Participants who have missing data points will be included in the analysis under a Missing at Random assumption implicit when using the longitudinal model. If there are more than 5% of participants who withdraw completely from the study or do not complete at least one post-baseline measurement, then we will undertake Multiple Imputations, again making a Missing at Random assumption. We will conduct an additional (sensitivity) analysis using controlled multiple imputation to examine the impact in case of Missing Not At Random (MNAR).

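### The protocol gives two conflicting rules for the missing-not-at-random analysis of CORE-OM, and one of them rests on a count that ignores loss at 7 and 12 months

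*Protocol article*

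**What the plan says.** Under Primary analyses, the mixed model is to "estimate the mean difference in CORE-OM between arms over 3-, 7- and 12-month follow-up trial assessments". Section {20a} limits the analysis set to randomised participants who "have at least one post-randomisation measure at the 3-month, 7-month or 12-month follow-up trial assessment".

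Two sections then deal with missing CORE-OM data:

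- Sensitivity analysis on primary notes that the model is valid under MAR and continues: "If the proportion of participants that have no post-randomisation measures is above 5%, we will conduct an additional analysis using controlled multiple imputation". The stated purpose is to examine MNAR.
- Section {20c} starts from a different condition, "If there are more than 5% of participants who withdraw completely from the study or do not complete at least one post-baseline measurement", and attaches a different action to it: "then we will undertake Multiple Imputations, again making a Missing at Random assumption". The next sentence stands alone: "We will conduct an additional (sensitivity) analysis using controlled multiple imputation to examine the impact in case of Missing Not At Random (MNAR".

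Section {18b} explains what complete withdrawal means for the data: "If a participant chooses to withdraw from all study procedures, no further outcome data will be collected". Scores given before withdrawal can still exist. On expected loss, Sample size {14} says "Previous small trials have reported 15–20% missing at follow-up", and separately allows for 10% of participants with no post-randomisation measure at all.

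**The concern.** The model needs MAR for every absent 3-, 7- or 12-month score, not only for people who give none. The rule under Sensitivity analysis on primary counts only the latter. A participant who answers at 3 months and is then lost does not count towards it, although two of that participant's three scores are missing.

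Late loss is a realistic prospect. The sample size section treats loss by the end of a trial and absence of any measure as two separate quantities. The 12-month assessment is in person, although questionnaires may be self-completed online ({18a}). Participants know their allocation ({17b}), so loss related to outcome could differ between arms.

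Section {20c} does not repair this clearly, because it gives a different count, a different action and no condition on the MNAR analysis. After the data are in, either section could be cited for running or omitting that analysis, and {17a} says the analysts are not blinded. At stake is whether the main untestable assumption behind the primary result gets examined.

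**Working it through.** **1. The plan's own figure.** Inputs from Sample size {14}: difference 5/34 = 0.147, SD 0.5, three measurements, correlation 0.35, 5% significance (two-sided assumed), 90% power, ratio 2:1.

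- SD of the time-average: 0.5 × √((1 + 2 × 0.35)/3) = 0.376.
- This gives 104 controls and 208 intervention, N = 312, with power 0.902.
- 104/0.85 = 122.35, rounded up to 123; 123 × 3 = 369.

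The design reproduces. It gives 369 × 3 = 1107 planned follow-up scores.

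**2. What the rule counts.** 5% of 369 is 18.45, so the rule is met at 19 participants with no measure and not at 18. Take 18 with none:

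- Extreme case, the other 351 give only a 3-month score: (3 × 18 + 2 × 351)/1107 = 756/1107 = 68% of scores missing. Rule silent.
- Assumed loss of 30% at 7 and 40% at 12 months: (18 + 110.7 + 147.6)/1107 = 25% missing. Rule silent.
- Assumed loss of 15% at 7 and 20% at 12 months, using the range cited from earlier trials: (18 + 55.35 + 73.8)/1107 = 13% missing. Rule silent.

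**3. When the rule would be met.** Binomial chance of 19 or more among 369, by true share with no measure:

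| Share with no measure | Chance rule is met |
|---|---|
| 2% | 0.0002 |
| 3% | 0.017 |
| 4% | 0.16 |
| 5% | 0.48 |
| 7% | 0.94 |
| 10% | 0.9997 |

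Loss at 7 and 12 months does not enter this table.

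**4. The two sections side by side.**

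| | Sensitivity analysis on primary | Section {20c} |
|---|---|---|
| Counted towards 5% | No post-randomisation measure | No post-baseline measure, or complete withdrawal |
| Action above 5% | Controlled imputation (MNAR) | Multiple imputation under MAR |
| MNAR analysis | Conditional | No condition stated |

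**5. Possible size of bias.** The loss and departure figures here are assumptions; the documents give none. Suppose unseen scores are δ item points worse than MAR predicts in both arms. The model recovers the difference without δ, so the bias is about δ × (share of scores missing in COS-P − share missing in TAU).

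Assume loss at 3/7/12 months of 4%/35%/45% in COS-P and 4%/20%/25% in TAU. The shares missing are 84/3 = 28.0% and 49/3 = 16.3%, a difference of 11.7 percentage points.

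| δ | δ × 0.117 | Large-sample simulation | Share of 0.147 |
|---|---|---|---|
| 0.15 | 0.018 | 0.018 | 12% |
| 0.25 | 0.029 | 0.029 | 20% |
| 0.50 | 0.058 | 0.058 | 40% |

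The benefit is overstated by these amounts. With the loss patterns swapped between arms, it is understated by 0.019, 0.027 and 0.057. With equal loss (4%/30%/40% in both arms), the simulated bias is within 0.002 of zero.

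**The case against.** A reader might infer that the MNAR analysis runs only above 5% and that late loss can never bring it about. That is true of Sensitivity analysis on primary read alone, not of the article. On its plain wording {20c} runs the analysis whatever the loss. If its last sentence is instead read as depending on the 5% clause, the withdrawal limb counts some people who leave after a 3-month score. Late loss then escapes only where visits are missed without withdrawal. This objection stands, and it limits the point to a conflict between sections plus a poor count in one of them.

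It can also be said that the gap does not arise under the plan's own budget. At 10% with no measure the rule is met with probability 0.9997, and nothing in the text then confines the imputation to people without any score. This stands too. The exposed case is good early response followed by poor later retention.

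On size, a reader might infer that a third of the target difference is at risk: 20% of all COS-P scores missing, 0.25 worse than MAR predicts and no departure in TAU gives 0.20 × 0.25 = 0.05, or 34% of 0.147. Those inputs are not in the documents and lie near the worst case. The same departure at 12 months only gives 0.05/3 = 0.017. Section {18b} also keeps people who stop only the intervention in follow-up, which limits loss tied to non-adherence.

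Lastly, a reader might see a contradiction between {20c}, which speaks of including all participants, and the analysis set in {20a}. That sentence concerns non-adherence, so it does not support the charge.

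The size of the departures and the imputation model can properly be left to the statistical analysis plan. The conflict between two published sections cannot be set aside on that ground.

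**Conclusion.** The point holds as a conflict in the published text. The two sections disagree on who counts towards 5%, on what follows, and on whether the MNAR analysis is conditional, so the article does not settle whether it will be run. The count under Sensitivity analysis on primary is also poorly matched to an estimate averaged over three visits, because it does not respond to missed 7- and 12-month scores.

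The practical gap is limited to trials where about 4% or fewer lack all follow-up while many miss later visits. Under the assumptions above, the untested bias would range from about zero, with equal loss and departure in both arms, to about 0.02–0.06 item points with differential loss, in either direction, against 0.147. This does not show that the primary analysis is biased. It shows that the safeguard might be omitted in a case where it is needed. The change should be made; it does not call the design into question.

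**What to change.** Under Sensitivity analysis on primary, remove the 5% condition from the MNAR analysis. State that controlled multiple imputation will be run routinely, over all randomised participants and all missing 3-, 7- and 12-month CORE-OM values, with departures from MAR allowed to differ by arm. Equal departures with similar loss would largely cancel and reveal little.

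Make {20c} say the same. If a 5% rule is kept there for the additional imputation under MAR, state its count once and make clear that the MNAR analysis does not depend on it. The range of departures can be set in the statistical analysis plan before data lock.

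The cost is a wording change in two sections and a little more analysis work. No extra data are needed and the sample size is unaffected.
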